### Evaluation

Various evaluation tools will be utilized at three time points (t_0_, t_1_, t_2_) to test the working hypotheses. Assessments of frailty [14, 22] and hearing ability will only be collected at t_0_, to verify the inclusion and exclusion criteria. Table 1 shows the timing of all measurements of individual diagnostic criteria.

**Table 1 Tab1:** Study overview regarding diagnostic measures and time points

time point	study period						
	enrollment	allocation	post-allocation			close-out	
	inclusion of LTC-facilities	statification randomization	pre-inter-vention (t_0_)	intervention	post-inter-vention (t_1_)	6-month follow up (t_2_)	intervention waiting group
**Enrollment**							
review of inclusion criteria of the LTC-facilities	X						
allocation of the LTC-facilities		X					
informed consent of the LTC-residents			X				
**Assessment**							
demografic and clinical data of the LTC-residents			X				
inclusion criteria of the LTC-residents: Clinical Frailty Scale			X				
inclusion criteria of the LTC-residents: speech audiometry			X				
*clinical assessments*							
cognitive ability: Dementia-Detection-Test (DemTect)			X		X	X	
language ability: Regensburg Word Fluency Test (RWT), semantic and phonological verbal fluency			X		X	X	
swallowing ability: Timed Test of Swallowing Capacity (TTSC)			X		X	X	
Questionnaire about every day Communication Practice– Communicative Activity Log (CAL)			X		X	X	
quality of everyday swallowing: Eating Assessment Tool (EAT-10)			X	X	X	X	X
*process evaluation*							
notes and protocols of the intervention process diary of the Residents				X			
evaluation of the intervention: feedback questionnaire for residents					X		
**intervention group**				X			
**control-waiting group**							X

#### Description of the study process

The OrkA project will be divided into three main phases: In phase 1, the intervention program will be prepared and the 12 LTC facilities in the project region will be recruited. Phase 2 will involve the recruitment of test subjects, administration of the status survey t_0_ in participating LTC facilities, implementation of the intervention in the participating facilities, and the follow-up survey t_1_. Subsequently, the follow-up survey t_2_ will be administered 6 months after the intervention, coinciding with the implementation of the intervention in the three control waiting facilities. In this second project phase, processes (i.e., the intervention with groups A and B, the intervention and testing with control waiting groups) will be staggered, due to the extensive scope of personnel work and process-related adjustments. This will ensure that the intervention can be carried out with the planned personnel (i.e., two speech language therapists), thereby minimizing any influence of personnel factors on the final results. Moreover, the process evaluation will allow for initial adjustments to be made, in the event that individual components (e.g., the control waiting design) lead to– for example– a high dropout rate.

Phase 3 will involve the summary process and evaluation of the intervention outcome. Table 1 shows the steps and time schedule.

#### Data processing and statistics

Data collected in the LTC facilities, test results, and data from the structured surveys will be saved (i.e., input) and analyzed using the Statistical Package for the Social Sciences for Windows (SPSS Inc., Chicago, IL/USA), in the version currently available at the Institute. The data will be stored on the secure servers of Hannover Medical School, and access to the data will be limited to the research team. For quality assurance, random checks of every fifth entry in the test protocols and plausibility checks will be carried out. Given the low risk of the preventive intervention, no external data monitoring committee is deemed necessary.

As part of the process analysis, meeting minutes and free-text answers to the surveys will be transcribed and pseudonymized. The research team are familiar with the recommendations for good scientific practice in qualitative research, with respect to data protection [23]. Any missing values will be replaced sensibly and conservatively.

Statistical significance will be determined by *p*-values < 0.05. Descriptive statistics will be employed to define frailty, hearing, swallowing, speech, cognitive abilities, and changes over time. A descriptive analysis will be conducted regarding the participating LTC facilities, the intervention study population, and the control waiting group. Additionally, a comparative analysis of central characteristics (i.e., gender distribution, age, frailty, etc.) will be carried out.

The primary endpoint will be evaluated at the individual level, according to the intention-to-treat principle. To detect statistically significant differences in the change in TTSC between groups at t_0_, t_1_, and t_2_, an unpaired t-test will be conducted with a two-sided significance level of 5%. Given a *p*-value < 0.05, any difference will be deemed statistically significant.

For the exploratory analysis of the secondary endpoints of language ability, subjective assessment of swallowing ability (according to the EAT-10), and communicative practice (according to the CAL), a comparative analysis will be conducted between the intervention and control waiting groups at t_0_, t_1_, and t_2_, using t-tests for unconnected samples [309]. A separate comparative analysis of the endpoints between measurement time points within the intervention group and the control waiting group will be conducted, using t-tests for connected samples.

Univariate and bivariate statistical procedures, as well as multivariable regression analyses (i.e., linear and logistic), will be used to assess possible associations between different dependent and independent variables, such as the influence of the LTC facility or sex. Continuous variables will be presented as means and standard deviations, while categorical variables will be presented as median and interquartile ranges.

The process evaluation will be based on an analysis of the documented frequency or continuity of active participation in the training units, the frequency of self-training, and the survey, which will be primarily evaluated quantitatively using univariate statistical methods (e.g., frequency counts, measures of central tendency, dispersion). In addition, subgroup analyses using bivariate statistical methods are planned (e.g., examination of a connection between participation frequency or dropout rate and the presence of mild to moderate frailty or dementia). Field notes, short minutes of sessions, and free-text information in the survey will undergo content analysis and topic evaluation [24].

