### Characterization of LTC facilities as clusters and participants

The intervention will be implemented in 12 LTC facilities in a group setting, with approximately eight subjects per group. Recruitment will follow a two-stage process. In the first stage, LTC facilities will be recruited. For this purpose, the central supporting organization will contact relevant LTC facilities and members of the research team will introduce the project (i.e., contents, scope of participation, data protection, etc.). Subsequently, interested LTC facilities will be sent detailed project descriptions, to ensure their free, open, and informed participation. The final set of LTC facilities will be determined on the basis of their informed consent of unit managers, number of beds, sponsorship structure (in Germany, facilities are run by profit (i.e., private) or non-profit (e.g., municipal or religious) organizations), and geographical location.

The following inclusion criteria will apply to LTC facilities: (i) located in the greater region of Hanover, (ii) structured by diverse sponsorships, and (iii) providing a regular range of activating group activities (e.g., movement and cognitive training as part of “usual care”). Gerontopsychiatric LTC facilities, facilities for the disabled, and exclusive day care facilities will be excluded. In accordance with cluster randomization recommendations [13], the 12 selected LTC facilities will be stratified by size, sponsorship structure, and resident characteristics, and then randomly distributed to either the intervention or the control waiting group.

In the second step, LTC facility coordinators will recruit 6–10 resident participants from their facility. Prior to this selection, members of the research team will introduce the project within each facility. Participation will be voluntary and will only begin after participants have received detailed information about the study objectives, procedures, and possible consequences, as well as their participant rights. Participants will be able to withdraw their consent at any time. The inclusion criteria for participation will be as follows:

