### Data collection

#### Sample size calculation

The primary outcome variable will be swallowing capacity, as measured via the Timed Test of Swallowing Capacity (TTSC). Based on a two-tailed unpaired t-test with a significance level set to 5% and a power of 80%, *n* = 5 clusters per group will be required (assuming *n* = 8 individuals per cluster). Anticipating a difference in the change in swallowing capacity of 2.8 ml/s between groups, with a pooled standard deviation of 3 ml/s [16] and an ICC of 0.1 [14, 15],^1^*n* = 10 clusters with a combined total of *n* = 80 individuals will be required.

Studies investigating individuals with pre-existing dysphagia in nursing homes [16] and nursing home residents, more generally [17], have reported dropout rates between 10 and 52%. According to the defined inclusion and exclusion criteria, the present study will address less vulnerable residents with no pre-existing dysphagia. Thus, a lower dropout rate of approximately 20% is assumed. On the basis of these assumptions, a sample size of approximately *n* = 100 participants in 10–12 clusters (i.e., 5–6 intervention facilities and 5–6 control waiting facilities) will be required.

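### The primary test is an individual-level unpaired t-test that ignores the randomised facilities; at the protocol's own ICC of 0.1 its true type I error is about 11–16%, not 5%

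*Protocol article*

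**What the plan says.** All statements are in the protocol article.

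- **Unit of randomisation** (Characterization of LTC facilities as clusters and participants): "the 12 selected LTC facilities will be stratified by size, sponsorship structure, and resident characteristics, and then randomly distributed" to intervention or waiting control. Each facility contributes 6 to 10 residents.
- **Sample size** (Sample size calculation): "Based on a two-tailed unpaired t-test with a significance level set to 5% and a power of 80" per cent; the section concludes that five "clusters per group will be required (assuming *n* = 8 individuals per cluster"). The effect is given as "Anticipating a difference in the change in swallowing capacity of 2.8 ml/s between groups". The variability and clustering assumptions come next in that section: "with a pooled standard deviation of 3 ml/s [16] and an ICC of 0.1". The result is 10 clusters and 80 residents. Allowing for about 20% dropout, this becomes about 100 residents in 10 to 12 clusters.
- **Primary analysis** (Data processing and statistics): "The primary endpoint will be evaluated at the individual level, according to the intention-to-treat principle". For the between-group difference in TTSC change, "an unpaired t-test will be conducted with a two-sided significance level of 5" per cent, and p < 0.05 counts as significant.
- **Secondary endpoints** (same section): described as exploratory and compared between arms with t-tests for independent samples.
- **Facility in the analysis** (same section): it appears only among regressions that look for possible associations, "such as the influence of the LTC facility or sex".

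**The concern.** An unpaired t-test on residents is valid only if residents are independent, that is, if the ICC is zero. The protocol itself assumes 0.1. The programme is also delivered in groups within facilities, so shared influences on outcome within a facility are plausible.

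Ignoring a positive ICC understates the standard error and credits the test with far more degrees of freedom than 10 or 12 randomised units can supply. Both errors act in one direction: intervals too narrow, p-values too small. The affected result is the single confirmatory one, so a significant finding could not be taken at its stated level.

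This is not a detail left to a later analysis plan. The article names the level of analysis, the test, the significance level and the decision rule.

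**Working it through.** **Inputs.** Difference 2.8 ml/s, SD 3 ml/s, ICC 0.1, m = 8 per facility, two-sided 5%, power 80%, dropout about 20% (Sample size calculation). 6 to 10 residents per facility and 12 facilities (Characterization of LTC facilities). The ICC is applied to the change score, as the protocol does.

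**1. The protocol's own figure reproduces.** Design effect DE = 1 + (m − 1) × ICC = 1 + 7 × 0.1 = 1.7. Three routes lead to 5 clusters per group:
- Individual t-test size inflated by DE: 19.03 per arm × 1.7 / 8 = 4.04, rounded up to 5.
- Normal approximation plus one cluster per arm: 18.02 × 1.7 / 8 + 1 = 4.83, rounded up to 5.
- t-test on cluster means, SD of a mean = 3 × √(1.7/8) = 1.383: power 66.7% with 4 per arm (6 df) and 80.0% with 5 per arm (8 df).

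80 / 0.8 = 100 residents, as stated. Every route adjusts for clustering. Without it, about 19 to 20 residents per arm would have been enough.

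**2. Type I error of the test as written.** The naive standard error is too small by a factor √DE, so the approximate true level is 2 × [1 − Φ(1.96/√DE)].

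| Residents analysed per facility | ICC | DE | True level |
|---|---|---|---|
| 6 | 0.1 | 1.50 | 11.0% |
| 6.4 (8 less 20%) | 0.1 | 1.54 | 11.4% |
| 8 | 0.1 | 1.70 | 13.3% |
| 10 | 0.1 | 1.90 | 15.5% |
| 8 | 0.05 (assumed) | 1.35 | 9.2% |
| 8 | 0.2 (assumed) | 2.40 | 20.6% |

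For m = 8 and ICC 0.1: 1.96/√1.7 = 1.503, and the two tails beyond 1.503 hold 13.3%.

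Simulation with a random facility effect (200,000 trials per setting, ICC 0.1) agrees. The individual-level t-test rejects in about 13.4% of trials with 5 or 6 facilities of 8 per arm, 11.0% with 6 facilities of 6 per arm, and 15.7% with 5 facilities of 10 per arm. A t-test on facility means stays at about 5.0% in each setting.

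**3. Confidence interval half-width, 12 facilities, SD 3.**
- 8 per facility (48 per arm). As written: 1.986 × 3 × √(2/48) = 1.22 ml/s. With clustering and 10 df: 2.228 × 3 × √(2 × 1.7/48) = 1.78 ml/s.
- 6.4 per facility (38.4 per arm). As written: 1.992 × 3 × √(2/38.4) = 1.36 ml/s. With clustering: 2.228 × 3 × √(2 × 1.54/38.4) = 1.89 ml/s.

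**4. Power of a cluster-respecting test** (non-central t on facility means).

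| Facilities | 8 analysed each | 6.4 analysed each |
|---|---|---|
| 12 | 88.4% | 84.3% |
| 10 | 80.0% | 75.0% |

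**The case against.** **Shorthand.** The sample size section also says unpaired t-test while using an ICC, so the term might stand for an adjusted test. This is weak: the statistics section specifies the individual level and names no adjustment.

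**The facility regressions.** A reader might take these as the correction, or might infer that facility is to be entered as a fixed covariate beside arm, which would leave the arm effect unidentifiable because each facility lies in one arm. The text supports neither reading. It lists facility next to sex in a search for associations, specifies no such model, and does not link it to the primary test.

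**What was powered.** A reader might infer from the 80.0% at 8 df that a cluster-level test was powered and then abandoned. The documents do not show this, because 5 clusters per group also follows from an individual-level t-test size times the design effect. What stands is narrower: the sample size allows for clustering and the stated test does not.

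**Stratification.** Stratifying on facility size, sponsorship and resident characteristics could reduce chance imbalance and bring the inflation below the figures above. By how much cannot be determined from the documents. It does not rescue a test that uses neither strata nor facility.

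**Unknown ICC.** The inflation depends on a planning value. That is fair, but any positive ICC makes the test anti-conservative, and 0.1 is the protocol's own choice.

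**Secondary endpoints.** They are exploratory and no ICC is given for them. The same kind of error applies, but its size is unknown.

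**Conclusion.** The point holds and should be fixed before analysis. Under the protocol's ICC of 0.1, the stated 5% primary test has a true type I error of about 13% with 8 residents per facility, 11.4% with 6.4 completers, and about 11% to 16% over the permitted 6 to 10. At an assumed ICC of 0.05 and 8 per facility it is still about 9%. The reported interval would be about two thirds of its proper width (1.22/1.78 = 0.69 with 12 facilities of 8).

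These figures assume equal facility sizes, normal facility effects, an ICC that applies to the change score, and no gain from stratification. They concern one comparison only; testing at several time points is a separate matter and is not included. The weight of the finding rests on the primary test alone.

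**What to change.** In Data processing and statistics, replace the unpaired t-test for the primary endpoint by one prespecified analysis that respects the randomised units. Choose either:

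- a linear mixed model on TTSC change with arm as a fixed effect, a random facility intercept, and Satterthwaite or Kenward-Roger degrees of freedom; or
- a t-test on facility means with (number of facilities − 2) degrees of freedom.

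These are alternatives. They weight facilities differently when sizes vary, so one must be named in advance. Use the same structure for the exploratory between-arm comparisons, and state that the facility regressions are exploratory and do not correct the primary test.

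**Cost.** The change is one of wording and needs no new data, but p-values and intervals become less favourable. Under the stated assumptions power stays at or above 80% with 12 facilities, even after 20% dropout. With 10 facilities it holds at 80% only if 8 residents per facility are analysed (for example, 10 recruited in each), and falls to 75% with 6.4. The sponsor should therefore secure 12 facilities rather than rely on the 10 to 12 now allowed.

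### The primary t-test follows neither the facility randomisation nor its strata; ignored clustering is the larger error, and the strata matter once clustering is handled

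*Protocol article*

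**What the plan says.** Under the characterisation of facilities and participants, "the 12 selected LTC facilities will be stratified by size, sponsorship structure, and resident characteristics" before random allocation to intervention or waiting group. The number of strata and their cut-points are not given.

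Under data processing and statistics, "The primary endpoint will be evaluated at the individual level, according to the intention-to-treat principle". For the between-group difference in TTSC change, "an unpaired t-test will be conducted with a two-sided significance level of 5" per cent. No term for facility or stratum is named. The regressions described later in that section mention the influence of the facility, but as explorations of association, not as the primary comparison.

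The sample size section does allow for clustering. It starts from a t-test ("Based on a two-tailed unpaired t-test with a significance level set to 5% and a power of 80" per cent), assumes a "difference in the change in swallowing capacity of 2.8 ml/s between groups", a "pooled standard deviation of 3 ml/s", an ICC of 0.1 and "8 individuals per cluster", and arrives at 5 clusters per group and 80 residents. Allowing for 20% dropout, it plans about 100 residents in 10–12 clusters.

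**The concern.** An analysis should respect the unit that was randomised and the restrictions placed on the allocation. Here it respects neither, and the two omissions pull in opposite directions.

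- **Facility left out.** Residents of one facility are treated as independent. The standard error is too small and false positives become too frequent.
- **Strata left out.** Stratified allocation removes between-stratum variance from the true variance of the arm difference, but an unstratified test still counts it as noise. The standard error is then too large and power is lost.

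In the test as written the first effect dominates. The second appears if the sponsor repairs clustering alone, for example by moving the same t-test to facility means. With only 10–12 facilities, both affect how far the primary p-value can be trusted.

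**Working it through.** **Inputs from the sample size section:** difference 2.8 ml/s, SD 3 (variance 9), ICC 0.1, 8 residents per cluster, 80 analysed. Between-facility variance is 0.1 × 9 = 0.9 and within-facility variance is 8.1. **Assumption, not in the document:** the share of between-facility variance explained by the strata, run from 0 to 100%, and the layout of the strata.

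**1. The plan's own figure.** n per arm = 2 × (1.960 + 0.842)² × 9 / 2.8² = 18.02, rounded up to 19. Design effect = 1 + (8 − 1) × 0.1 = 1.7. Then 19 × 1.7 = 32.3 and 32.3 / 8 = 4.04, so 5 clusters per arm and 80 residents; 80 / 0.8 = 100. A cluster-level t-test with 8 degrees of freedom has 80.0% power at 5 per arm and 88.4% at 6 per arm. The stated figures reproduce.

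**2. The test as written.** Its standard error is too small by √1.7 = 1.30. Type I error ≈ 2 × [1 − Φ(1.96 / 1.304)] = 13.3%; simulation gives 13.1–13.4%. At ICC 0.02, 0.05 and 0.2 the simulated values are 6.8%, 9.4% and 20.6%.

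Adding strata to this resident-level test and nothing else (simulation, 6 facilities per arm, 8 residents each, matched-pair strata):

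| Share explained | Type I error, without → with strata | Power at 2.8 ml/s |
|---|---|---|
| 0% | 13.1 → 13.7% | 97.7 → 97.9% |
| 50% | 8.9 → 9.8% | 98.7 → 98.9% |
| 75% | 6.5 → 7.5% | 99.3 → 99.4% |
| 100% | 4.0 → 4.9% | 99.7 → 99.7% |

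Power gains are at most 0.2 points (0.3 with 5 per arm), and an inflated error rate gets slightly worse.

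**3. Facility accounted for, strata left out.** With 12 facilities and 80 analysed, 80 / 12 = 6.67 residents each. Variance of a facility mean = 0.9 + 8.1 / 6.67 = 2.115. Simulation on 12 facility means with one two-level factor balanced across arms:

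| Share explained | Type I error without the factor | Power at 2.8 ml/s, without → with |
|---|---|---|
| 0% | 5% | 85.2 → 84.3% |
| 25% | 3.8% | 85.7 → 88.0% |
| 50% | 2.7% | 86.5 → 91.5% |
| 75% | 1.7% | 87.3 → 94.8% |

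With the factor included, type I error is 4.9–5.1% throughout. Repeat runs agree to about 0.1 points for error rates and 0.3 for power.

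Hand check at 50%: the true variance is 2.115 − 0.45 = 1.665. The unadjusted estimate averages 1.665 + 0.45 × 6/5 = 2.205. The effective critical value is 2.228 × √(2.205 / 1.665) = 2.564, and the two-sided tail of t with 10 df beyond it is 2.8%.

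**4. Cost if the factors explain nothing.** Each balanced facility-level factor takes one degree of freedom.

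- 12 facilities: standard error √(2 × 2.115 / 6) = 0.840 and noncentrality 2.8 / 0.840 = 3.33. Power at 10, 9 and 8 df is 85.1%, 84.2% and 83.1%.
- 10 facilities, 8 residents each: facility-mean variance 0.9 + 8.1 / 8 = 1.9125, standard error 0.875, noncentrality 3.20. Power at 8, 7 and 6 df is 80.0%, 78.4% and 76.0%.
- Three facility-level terms, by simulation: 85.2 → 81.5% with 12 facilities, 80.1 → 72.7% with 10.

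**The case against.** A reader might infer that the planned t-test is too conservative and loses power because it drops the strata. The documents do not support that. The quoted test is run on residents, and at the plan's own ICC its standard error is too small. It turns conservative only if the strata explain nearly all between-facility variance, and its nominal power is already about 98%. The conservative effect belongs to a test that the protocol does not yet contain.

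Three further objections have force:

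- Nothing in the document shows that bed numbers or sponsorship predict change in TTSC, so the 25–75% range is illustrative.
- Adjustment is not free with so few clusters. Matched-pair strata at facility level, 6 per arm, lower power from 88.7% to 80.0% if uninformative, and from 90.6% to 88.7% even at 50% explained.
- Residents' t0 values cannot stand in for the resident characteristics used in stratification, because Table 1 places allocation before resident consent and t0.

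All three stand and limit the remedy. It might also be said that covariates are commonly left to an analysis plan. That does not answer the point: the article names the primary test, and an unpaired t-test has no place for facility or stratum.

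**Conclusion.** The point holds as a mismatch between randomisation and primary analysis, with two parts of unequal weight. Ignored clustering comes first: about 13% type I error instead of 5% at ICC 0.1 and 8 residents per facility if the strata explain nothing, and still about 6% if they explain 75%. Omitted strata come second, and only once facility is accounted for. The consequence is then a conservative test and a power loss that depends on an explained share the document does not give. That part cannot create a false positive claim. It still belongs in the same correction, because a repair of clustering alone would leave it in place, and because picking adjustment factors after seeing 10–12 facility results would invite selection.

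**What to change.** Replace the resident-level t-test as the primary analysis by one of:

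- a facility-level analysis, or a mixed model with a random facility effect, using facility-level degrees of freedom and one or at most two prespecified allocation factors with one degree of freedom each (size, sponsorship structure); or
- a permutation test that re-allocates facilities within the strata actually used.

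Apply the same structure to the secondary between-group comparisons. Residents' t0 values may be added as ordinary baseline adjustment, described as such and not as a substitute for the strata. Stratum terms should not be added to the present t-test without accounting for facility.

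The change is to wording and can be made before outcome data are examined. If the factors prove uninformative, it costs about 1 point of power for one factor and 2 for two with 12 facilities. With 10 facilities the cost is about 1.6 and 4 points, starting from a planned power of only 80%. The plan should state this trade-off when it fixes the number of factors.

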### Main hypothesis

The orofaciopharyngeal and speech-communication program will help to prevent a decline of swallowing skills in older individuals.

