In addition to the above-described self-assessment tools, some additional questionnaires will be filled in by nursing staff: the Clinical Frailty Scale (CFS) [1, 4], to record patients’ degree of frailty (considering physical, cognitive, and psychological dimensions); and the “Double Surprise Question” [29], to capture life expectancy.

Positive intervention results for swallowing functions and/or communication skills are expected to prompt the implementation and offer of preventive group training programs with respect to swallowing, speech, and language, not only in LTC facilities but also with older individuals, in general.

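### The primary TTSC analysis names three visits at a full 5% level but no primary contrast; if success at either t1 or t2 can support the main hypothesis, the family-wise error is about 9%, not 5%

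*Protocol article*

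**What the plan says.** The main hypothesis is that the programme "will help to prevent a decline of swallowing skills in older individuals"; it gives no time point. TTSC is named as the primary endpoint, again without a visit, and Table 1 schedules it at t0, t1 and t2 without ranking them.

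The analysis sentence under Data processing and statistics reads: "differences in the change in TTSC between groups at t_0_, t_1_, and t_2_, an unpaired t-test will be conducted", at a two-sided 5% level. The next sentence says that, with p < 0.05, "any difference will be deemed statistically significant". No order of testing, division of alpha or requirement that both visits succeed is given.

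The Sample size calculation is built on one contrast: "Anticipating a difference in the change in swallowing capacity of 2.8 ml/s between groups". It does not say over which interval that change is measured. Only the secondary endpoints are labelled exploratory.

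**The concern.** The analysis sentence cannot be carried out as written. A change needs two visits, so there is none at t0. After baseline there are two changes, t0 to t1 and t0 to t2, and each needs its own unpaired t-test. At least two primary tests are therefore implied, each at the full 5%, and nothing says which one answers the main hypothesis.

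The two contrasts ask different questions: t1 measures the effect at the end of the programme, and t2 whether it persists six months later. If the choice is left open until the data are in, a favourable result at either visit could be presented as the primary finding, and the stated 5% would no longer describe the risk of a false claim. The 80% power has the same gap, because it belongs to one contrast that is never identified.

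**Working it through.** **Inputs from the Sample size calculation.** Difference in change 2.8 ml/s, SD 3 ml/s, ICC 0.1, 8 residents per cluster, two-sided 5%, power 80%, dropout 20%.

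**1. The plan's own figure.**
- Per arm without clustering: 2 × [3 × (1.960 + 0.842) / 2.8]² = 18.0, rounded up to 19.
- Design effect: 1 + (8 − 1) × 0.1 = 1.7. Then 19 × 1.7 = 32.3 per arm, and 32.3 / 8 = 4.04, rounded up to 5 clusters per arm.
- Check with a cluster-level t-test: the variance of the arm difference is 2 × 9 × 1.7 / (8 × 5) = 0.765, the noncentrality is 2.8 / √0.765 = 3.20, and with 8 degrees of freedom the power is 0.80. Four clusters per arm give 0.67.
- Dropout: 80 / (1 − 0.20) = 100.

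The stated 5 clusters per arm, 80 residents and about 100 after dropout reproduce. They spend the whole 5% on one test.

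**2. Correlation between the two changes.** The documents give none. If the variance is equal at all visits and every pair of visits has the same correlation w, then each change has variance 2σ²(1 − w) and their covariance is σ²(1 − w). The shared baseline therefore makes the correlation 0.5 whatever w is. If correlation instead decays with the number of visits between measurements (AR(1)), it is √(1 + w) / 2, which is 0.61 at w = 0.5 and 0.67 at w = 0.8.

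**3. Chance of at least one false positive.** Assume no effect at either visit, two tests that each truly hold 5%, and success at either visit counting. If the tests were independent: 1 − 0.95² = 9.75%. With correlation (bivariate normal, |Z| > 1.96 on at least one):

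| Correlation | Family-wise error |
|---|---|
| 0 | 9.75% |
| 0.3 | 9.5% |
| 0.5 | 9.1% |
| 0.7 | 8.3% |
| 0.8 | 7.8% |
| 0.9 | 7.0% |

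The AR(1) cases give 8.5 to 8.7%. A simulation of cluster-level t-tests with equal visit correlations gives 9.2% with 5 clusters per arm and 9.3% with 6, so the small number of clusters hardly alters the result.

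**4. Ways to restore 5%.** With one named contrast, or two tested in fixed sequence, the error is 5% and the first contrast keeps power 0.80 (5 clusters per arm). With both visits tested at 0.025, the family-wise error is 4.0 to 4.9% (correlation 0.8 to 0), but power per contrast falls to 0.67 with 5 clusters per arm and 0.79 with 6.

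**5. Status of t2.** The text under Secondary hypotheses offers the programme to the waiting group after t2, and only if it proves successful. Description of the study process has t2 coincide with delivery of the programme in the waiting facilities. On the second account, it is unclear whether the control arm is still untreated at t2.

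**The case against.** The sentence containing "any difference will be deemed statistically significant" is conditional on p < 0.05 and can be read as an ordinary definition of significance. It does not say that significance at one visit makes the trial positive. The test is also written in the singular, the sample size powers one difference, and the three visits could simply list when the measurements are taken. **This stands in part.** An either-visit success rule is permitted by the text, not stated in it, so the 9% must be conditional. But the mildest reading still leaves the interval of the primary change unnamed.

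An analysis plan that is not shown might settle the matter. That would answer mere silence. Here the article states a primary test and a significance rule without deferring either, and the visit at which the primary endpoint is judged defines the trial's main question.

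Three stronger readings are tempting and are not supported:
- A reader might count a t0 comparison as a third primary test, which would raise the error to 12.5 to 13.2%. The endpoint is a change, and none exists at t0.
- A reader might add the inflation from an individual-level t-test in a cluster trial. That is a separate defect and would make the multiplicity problem look larger than it is.
- A reader might extend the point to the communication outcomes, because the Discussion hopes for uptake on those too. The analysis section already calls the secondary endpoints exploratory.

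**Conclusion.** The point holds as a failure to fix the primary contrast. The article implies at least two primary comparisons at 5% each, names neither as primary, and ties its 2.8 ml/s and 80% power to neither. If a significant result at either t1 or t2 may support the main hypothesis, the family-wise error is about 9% instead of 5%.

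That figure is not in the documents. It assumes exactly two change contrasts, no effect at either visit, tests that are otherwise valid, and a correlation near 0.5; correlations from 0.9 to 0 give 7 to 10%. It would be wrong to infer that the plan declares an either-visit rule or that its error is unconditionally 9%. The sample size arithmetic itself is sound for a single contrast.

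**What to change.** 1. Name one primary contrast before any outcome data are compared: the change from t0 to t1, or the change from t0 to t2. State that the 2.8 ml/s and the 80% power refer to it.
2. Test the other visit at 5% only if the first contrast is significant (fixed sequence).
3. Remove t0 from the list of primary comparisons and treat any t0 comparison as descriptive.
4. Reconcile the two statements on when the waiting group receives the programme relative to t2 before t2 is used as a controlled contrast.

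The planned number of clusters and residents is unchanged, and a change-score comparison can be kept. The cost is the second chance of a positive result. There is also a substantive choice to make: whether the trial is chiefly about the effect at the end of the programme or its persistence at six months. If 2.8 ml/s was derived for one of these intervals, that should be stated, since it may not carry over to the other.
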